### Recruitment, compliance, and follow-up

All ED and PICU staff will be made aware of the study through information sessions, posters in the ED and PICU, weekly rounds with the research assistants, and weekly emails. Monthly recruitment newsletters will be sent to all sites to encourage enrollment and discuss commonly encountered questions.

Compliance is likely to be high as the protocol is simple and closely follows usual clinical practice in these patients. This assumption is based on experience from the Vasopressin in Pediatric Shock (VIP) study, which randomized children in vasodilatory shock to vasopressin or placebo and used many of the same sites and investigators as our current proposal. Despite utilizing a more complex protocol and recruiting sicker patients, the VIP trial had only two protocol violations and was successfully completed [32]. It is possible that open-label corticosteroid use will be higher than the anticipated 10 % rate. However, we will collect specific data on the circumstances in which this occurs in order to provide more targeted education around this practice in the full trial. Follow-up for the STRIPES pilot study ends at hospital discharge or death. Therefore, we anticipate a follow-up rate of 100 %.

### Data collection and management

Data for each patient will be entered by trained research assistants at each site and managed using an electronic data capture tool, REDCap (Research Electronic Data Capture), which will be hosted at the Children’s Hospital of Eastern Ontario (CHEO) Clinical Research Unit [33]. REDCap is a secure, web-based application designed to support data collection for research studies. Predefined ranges for all data values will be set up in this application to allow data entry personnel to validate data as soon as it is entered and send data queries immediately. Missing data will be similarly managed. For each enrolled patient, we will collect information from their medical chart. Data will be entered into the case report form (CRF, available on the STRIPES study website at http://stripes.ccctg.ca/Home.aspx), and each record will be identified only by study ID number to maintain patient confidentiality. The following information will be collected: demographic information, inotrope use, duration of mechanical ventilation, PRISM III and PELOD-2 scores, insulin infusion use, gastrointestinal bleeding, laboratory results, and basic resource utilization data. Research assistants at each site will maintain a daily paper screening log which will track every patient who is started on a vasoactive infusion within their first 24 h of PICU admission. When eligible patients are not enrolled, we will classify the reason for non-enrollment as: (1) refusal from patient and/or legal guardian (specifying reason for refusal, if provided); (2) inability to contact legal guardian in centers without deferred consent (specifying reason contact could not be made, if available); (3) refusal from attending physician (specifying reason for refusal); (4) lack of availability of the research assistant; and (5) patient died before enrollment. We will also record age, gender, and PRISM III scores for these patients to determine if there are demographic differences between eligible patients who are and are not enrolled. A data management plan has been developed for the study and is available on the STRIPES study website.

### Statistical analysis

To meet the feasibility objectives of this pilot RCT, we have planned descriptive analyses. We will present recruitment rate, feasibility events, and open-label corticosteroid use as proportions with 95 % confidence intervals. Recruitment feasibility will be defined as achieving 80 % of our target goal of 72 patients. We will present continuous data as means and standard deviations, or medians and interquartile ranges, as appropriate. Patients who are randomized but withdraw or do not provide consent will be analyzed using intention to treat if they provided consent to keep their data.

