**Methods/design:**

Steroids in Fluid and/or Vasoactive Infusion Dependent Pediatric Shock (STRIPES) is a pragmatic, seven-center, double-blind, pilot RCT. We aim to randomize 72 pediatric patients with fluid and vasoactive infusion dependent shock to receive either hydrocortisone or a saline placebo for 7 days or until clinical stability, whichever occurs first. The primary outcome of this pilot trial is the feasibility of recruitment, defined as the number of patients enrolled over a 1-year period. Secondary outcomes include the frequency of, and reasons for, open-label steroid use, protocol adherence, incidence of mortality and corticosteroid-associated adverse events, time to discontinuation of inotropes, and feasibility of blood sampling.

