Primary outcome	Patient accrual rate over a 1-year recruitment period
Key secondary outcomes	Adherence to the study protocol; frequency of open-label corticosteroid use and the clinical characteristic of patients in whom open-label corticosteroids are used; incidence of mortality and adverse events; time to discontinuation of inotropes; and the feasibility of mechanistic blood sampling

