### Outcomes

This is a pilot study; hence, the primary outcome is feasibility, defined by accrual rate over 1 year. Our goal is to recruit 72 patients within this time frame. However, we will consider patient accrual to be adequate if we recruit 60 patients from seven sites within 1 year. We will also assess potential barriers to recruitment, including lack of a deferred consent model, physician- and guardian-related consent issues, availability of research personnel, and the narrow recruitment window (6 h from the initiation of vasoactive infusion). The secondary outcomes are summarized in Table 3; they include the frequency of open-label steroid use, adverse events related to corticosteroid use, time to discontinuation of vasoactive infusions, incidence of mortality, and the feasibility of blood sampling.

**Table 3 Tab3:** Secondary outcomes for the STRIPES pilot study

Outcome	Metric for analysis
Adherence to the protocol:	We will consider adherence adequate if each of goals a through c is met in 80 % of enrolled patients:
a. Time to administration of the first dose of study drug b. Weaning of drug to q8h when hemodynamically stable c. Discontinuation of drug when off all vasoactive infusions	a. Goal is <8 h from starting vasoactive medication b. Goal is to wean within 12 h of no escalation of therapy c. Goal is to discontinue between 12 and 18 h after vasoactive infusion stopped
Open-label steroid use	We will consider the number of patients started on open-label steroids to be acceptable if it occurs in <10 % of patients
Clinical outcomes:	
a. Adverse events b. Clinical endpoints	a. Severe bleeding, secondary infections, and use of insulin infusions b. Time to discontinuation of vasoactive infusion and incidence of mortality
Successful blood sampling and processing	The percentage of patients from whom blood samples are sent
	The percentage of samples sent that are successfully received and analyzed in their respective labs

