### Sample size

Based on data from our multi-center retrospective study, we expect to enroll 72 patients. This target takes into account the frequency of septic shock at each center, along with the projected consent rate at each center. This target number will: (1) allow us to assess our feasibility objectives over a reasonable time period (1 year), (2) allow each center to recruit between 6 and 24 patients, and (3) allow us to test the acceptability of our eligibility criteria as well as open-label steroid use at seven sites and with exposure to 50 different clinicians. Given that this is a pilot study, we will consider recruitment to be feasible if we achieve 80 % (60 patients) of our target enrollment, a threshold commonly used in critical care pilot studies. With 60 patients, we will have the ability to detect an adherence rate of 80 ± 10 % (meaning 80 ± 10 % of study patients will have fewer than 10 % of monitored values as violations). The median time to discontinuation of vasoactive agents observed in this pilot study will be used to better estimate the sample size needed for the full RCT.

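### The primary outcome is a number of patients per year, but the analysis section reports it as a proportion with no named denominator, so on either plausible reading it gets no valid confidence interval

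*Protocol article*

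**What the plan says.** The protocol article defines the primary outcome three times, each time as patients over time. The Abstract gives "feasibility of recruitment, defined as the number of patients enrolled over a 1-year period". Table 1 gives "Patient accrual rate over a 1-year recruitment period". The Outcomes section says "the primary outcome is feasibility, defined by accrual rate over 1 year".

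The success criterion is also a count. The Outcomes section sets the goal ("Our goal is to recruit 72 patients within this time frame") and the minimum: "we will consider patient accrual to be adequate if we recruit 60 patients from seven sites within 1 year". The Sample size section repeats the minimum as a percentage of the target: "we will consider recruitment to be feasible if we achieve 80 % (60 patients) of our target enrollment".

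The Statistical analysis section then fixes the summary measure: "We will present recruitment rate, feasibility events, and open-label corticosteroid use as proportions with 95 % confidence intervals". The next sentence is "Recruitment feasibility will be defined as achieving 80 % of our target goal of 72 patients". Neither sentence says what the recruitment rate is divided by, and no interval for a count per unit of time is planned.

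**The concern.** A proportion needs a number of units that could each have been a success or a failure. A yearly enrolment count has no such number. Two candidates can be found in the article, and neither gives an interval for the primary outcome.

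- **The target of 72.** This is a planning figure, not 72 children each observed to enrol or not. A binomial interval on it treats 72 as a fixed ceiling and ignores that the number of arrivals is itself random.
- **The eligible patients.** The screening log described under Data collection and management could supply them. The result is the fraction of eligible children who are enrolled. That is a useful quantity, but it is not patients per year, and the 60-patient criterion cannot be applied to it.

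At stake is how precisely the accrual rate is reported. The Discussion presents the pilot as a source of feasibility data for planning the larger trial, and the accrual rate is its primary result.

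**Working it through.** **Inputs.** Target 72, minimum 60 and one year of recruitment (Outcomes; Sample size); 95 % confidence level and summary as a proportion (Statistical analysis). The number of eligible patients is not given, so it is varied below.

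**The plan's own figures.** 0.80 × 72 = 57.6, and 60/72 = 83.3 %, so the minimum of 60 is a rounded-up form of 80 % of the target. The difference between 58 and 60 is a separate matter and plays no part here. For adherence, which is a true proportion, the stated precision reproduces: 1.96 × √(0.8 × 0.2/60) = 0.101, that is 80 ± 10 %. So the binomial approach suits adherence; the question is whether it suits recruitment.

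**Reading 1: denominator 72.** For x patients enrolled in one year:

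- Exact Poisson limits: χ²(0.025; 2x)/2 and χ²(0.975; 2x + 2)/2.
- Exact binomial (Clopper-Pearson) limits for x/72, multiplied by 72 to return to patients a year.

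| Enrolled | Binomial on 72 (patients/year) | Width | Exact Poisson (patients/year) | Width | Width ratio |
|---|---|---|---|---|---|
| 60 | 52.3 to 65.6 | 13.2 | 45.8 to 77.2 | 31.4 | 2.4 |
| 66 | 59.6 to 69.8 | 10.2 | 51.0 to 84.0 | 32.9 | 3.2 |
| 72 | 68.4 to 72.0 | 3.6 | 56.3 to 90.7 | 34.3 | 9.5 |

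The choice of binomial method matters little at 60: the Wilson interval is 52.6 to 64.9 (width 12.3, ratio 2.6). At 72 the normal-approximation interval has zero width.

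Standard errors show the reason. For a Poisson count the standard error is √x. For the binomial version it is √(72 × x/72 × (1 − x/72)) = √(x(1 − x/72)). Their ratio is 1/√(1 − x/72). At x = 60 this is √60/√10 = 7.75/3.16 = 2.45; at x = 66 it is √12 = 3.46; at x = 72 it is unbounded. The binomial interval therefore shrinks as enrolment approaches the target, while the uncertainty in a yearly count does not.

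**Reading 2: denominator eligible patients.** With 60 enrolled and the eligible number assumed, the Clopper-Pearson intervals are:

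- 60/100: 49.7 % to 69.7 %
- 60/150: 32.1 % to 48.3 %
- 60/300: 15.6 % to 25.0 %

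These are valid intervals for the enrolment fraction. The same 60 patients in a year give very different percentages, so none of them describes patients per year.

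**The case against.** The strongest reply is that the harmful reading is inferred. The sentence names no denominator and no interval method, and the sentence after it, which mentions 72, states the success rule rather than an interval. The other items in the same list are ordinary patient-level proportions, the screening log records everyone started on a vasoactive infusion within the first 24 h of PICU admission, and the Discussion says eligible children who are not randomized will be counted. On that evidence enrolled/eligible is a plausible meaning, and a binomial interval for it is sound. This stands: the width figures apply only if 72 is the denominator. It does not rescue the sentence, because on that reading the primary outcome is left without an interval.

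A reader might infer that the narrow interval decides whether the trial is called feasible. The documents do not support that. Every stated criterion compares the observed count with 60 or with 80 % of 72, and none uses a confidence limit. Nor do they say that an accrual interval sets the size of the full trial: the only sample-size input that the Sample size section names is the median time to stopping vasoactive agents.

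A reader might also argue that a binomial interval would often be impossible because enrolment would pass 72. If the true rate were 72 a year, a Poisson count would exceed 72 with probability 0.47, but only on the assumption that enrolment continues beyond the target. The article gives 72 as the target sample size and does not say that it would.

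Finally, detailed interval methods may sit in an analysis plan that is not shown. That would excuse silence. Here the article states the type of summary, and the type does not fit the outcome.

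**Conclusion.** The point holds in a limited form. The protocol commits to a summary of the wrong type for its primary outcome. If 72 is the denominator, the 95 % interval is about 2.4 times too narrow at the 60-patient minimum and nearly vanishes at 72. If eligible patients are the denominator, the interval is correct but belongs to a different quantity. Either way there is no valid interval for patients per year.

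The feasibility decision is unaffected. The consequence is confined to the reported precision of the accrual rate that later planners would use.

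The Poisson figures assume Poisson arrivals over a fixed period of one year. Variation between sites beyond Poisson would widen the correct interval. If enrolment stops on reaching 72, the matching interval is one for the time to a fixed count.

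**What to change.** In the Statistical analysis section:

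1. Take the recruitment rate out of the list of proportions.
2. Report the primary outcome as patients enrolled divided by recruitment time, with an exact Poisson 95 % interval. Give it per year and also per active site-month, because the Trial status section shows sites opening between July 2014 and the fall of 2015. State that the interval assumes Poisson arrivals and may be too narrow if sites differ. If recruitment stops at 72, use the interval for time to a fixed count instead.
3. Report enrolled/eligible from the screening log separately, as a proportion with a binomial interval, labelled as the enrolment fraction and not as the primary outcome.

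The cost is a small change of wording. It needs only the enrolment count, the site opening dates and the screening log, which the trial already holds. The downside is a wider and less favourable interval for the accrual rate.

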### Monitoring

The Data Monitoring and Safety Committee (DMSC) will include a senior biostatistician, a pediatric endocrinologist, and a pediatric intensive care specialist. The DMSC will review all serious adverse events (SAEs) — any serious events that the attending site intensivist believes may be directly related to enrollment in this trial. Study sites will report all SAEs to the Coordinating Center within 24 h of becoming aware of the event. The site will fill out a SAE report and provide any related clinical documentation (de-identified) to the Coordinating Center for distribution to the Principal Investigator and the DMSC chair. The DMSC chair will determine whether immediate input from other DMSC members is required before sending the final DMSC determination to the Principal Investigator. There will be no stopping rules; however, the DMSC can make recommendations to the Principal Investigator, who will communicate back to the Steering Committee at the end of the trial regarding any safety concerns for the full trial. We will provide the DMSC with analyses by group (blinded as group A and B) at the completion of this pilot RCT. These analyses will include relative rates of gastrointestinal bleeding, infections, and hospital mortality. Due to the small sample size and short duration of this pilot trial, we have not planned for any interim analyses.

The study coordinator will monitor the sites at study initiation, midway through the recruitment period, and at study close-out to ensure compliance with the protocol and to troubleshoot any barriers to recruitment. Data entered into the electronic CRF will be verified on an ongoing basis, and the Data Quality function in REDCap will be used to send and resolve data queries where required. Given the pilot nature of this study, a formal audit of the trial will not be conducted.

### Ethics

Research ethics board approval has been obtained from all participating centers. Protocol amendments will be communicated as necessary to those involved with the study. An application for deferred consent was approved at five sites (Ottawa, Vancouver, Calgary, Hamilton, and Halifax). Deferred consent was not possible in Quebec as per provincial legislation. The study protocol was approved by the following ethics review boards: the Children’s Hospital of Eastern Ontario Research Ethics Board, Ottawa, Ontario (reference number: 14/05E); the Hamilton Integrated Research Ethics Board, Hamilton, Ontario (reference number: 14–636); Comité d’éthique de la recherche à CHU Sainte-Justine, Montreal, Quebec (reference number: 3990); the Montreal Children’s Hospital Research Ethics Board, Montreal, Quebec (reference number: 14-121-PED); the Conjoint Health Research Ethics Board of the University of Calgary, Calgary, Alberta (reference number: REB14-0606); the University of British Columbia Children’s and Women’s Research Ethics Board, Vancouver, British Columbia (reference number: H14-01109); and the IWK Research Ethics Board in Halifax, Nova Scotia (reference number: 1017182).

### Close-out

All data and source documentation will be stored in a locked, secure storage facility for 25 years from the time of study close-out. The study drug will be destroyed and reconciled at each site according to the procedures of the site pharmacy. Only the Principal Investigator, the research coordinator, or their delegate will have access to the data once the study is closed.

## Discussion

We recently published a systematic review [6] on the use of corticosteroids in pediatric shock. The review concluded that “The literature on the use of steroids in pediatric shock is limited in amount, methodological quality and demonstrates conflicting results. The limited evidence on which current guidelines are based strongly supports the need for a well-designed, pragmatic randomized controlled trial on the use of steroids in pediatric shock to inform future guidelines.” There are two small RCTs currently listed on www.clinicaltrials.gov (NCT01047670, NCT00732277); however, neither study has been updated since 2010. Given their size and unclear recruitment status, it is unlikely that either of the latter two trials will be able to answer the question of whether corticosteroids improve outcomes in pediatric shock.

This study is the first step towards a large RCT to provide clarity on the use of corticosteroids in critically ill children with shock. Results of the STRIPES pilot study will provide essential feasibility data for planning and conducting a larger, multi-center trial that will help to establish the role of corticosteroids in children with fluid and vasoactive infusion dependent shock. Our goal is to enroll a minimum of 60 patients at seven sites over a 1-year period. Failure to do so will prompt us to modify our plans for a future trial. If our recruitment rate is as anticipated or better, we will not modify eligibility criteria. If our recruitment rate is marginal (that is, barely achieves our goals), we will examine the number of patients excluded on the basis of each exclusion criterion, and will reconsider the necessity for any criterion that has resulted in a large number of excluded patients. We will record the number of eligible non-randomized patients and reasons for non-enrollment, and on the basis of these results, we will consider deterrents to randomization and methods to enhance enrollment of eligible patients. If the pilot study demonstrates feasibility, no major protocol changes are needed, and no safety concerns are raised by the STRIPES DMSC, then the results of the pilot study will be rolled into the full trial. However, if any of the above criteria are not met, then the protocol will be re-evaluated and the feasibility results of the pilot study published independently.

### Trial status

Recruitment for the STRIPES pilot study started at the Coordinating Centre (Children's Hospital of Eastern Ontario, Ottawa) in July 2014. Four of the six other Canadian PICUs initiated recruitment between December 2014 and February 2015. The remaining two sites will commence recruitment in July of 2015 and in the fall of 2015, respectively. The first patient was enrolled on September 4, 2014, and recruitment is expected to continue until March of 2016.

## Abbreviations

DMSC: Data Monitoring and Safety Committee
ED: emergency department
IV: intravenous
PELOD: pediatric logistic organ dysfunction
PICU: pediatric intensive care unit
PRISM: pediatric risk of mortality
RCT: randomized controlled trial
REB: Research Ethics Board
STRIPES: Steroid Use in Fluid and Vasoactive Infusion Dependent Shock
VIP: Vasopressin in Pediatric Shock
